### 5.1.2 Dosing regimen

In this clinical study, additional 9 subjects are planned to be enrolled, and a total of 1 dose group, 7.5×10^10^ vg, is set. After one subject is enrolled first and no significant toxic and side effects are observed within 14 days after administration, the study in the second subject may be initiated. After the second subject completes administration and no significant toxic and side effects are observed within 14 days, the study in the third subject may be initiated; and so on. While conducting safety study, lacrimal fluid and blood samples are collected from subjects to detect DNA of rAAV2/8 virus and immune responses against the therapeutic vector.

### 5.1.3 Packaging and labeling

Packaging: The investigational drug is packaged by the cooperative unit.

Labeling: The label should be indicated with product name, batch number, strength, shelf life, storage condition, entrusting party, manufacturer, "For clinical study use only", etc.

### 5.1.4 Drug storage and management

The investigational drug will be uniformly transported by the sponsor, and directly distributed to the study site by a specially-assigned person. According to the complete drug receipt procedures of the study site, there is a specially-assigned person to accept the drug and sign the drug receipt form.

The study site has established a strict drug management system (specially-assigned person, special cabinet and locked storage) to be responsible for the storage and distribution of investigational drug and establish the registration system. The study site should ensure that the storage environmental conditions (temperature, light, humidity, etc.) of investigational drug are compliant with regulations, and it should be recorded and stored. If the storage conditions are found beyond the specified range, contact the sponsor immediately.

Use of medications should be recorded on the appropriate log sheet.

At the end of the study, all investigational drugs, including all unused, partially used study drug and all drug packages returned, with completed and signed drug return log, at the investigator should be returned to the sponsor.

## 5.2 Concomitant Therapies

**5.2.1 Permitted concomitant therapies**

The following concomitant therapies are permitted during the study, including the screening period. All concomitant medications received by the subjects and reasons for medication (generic name, purpose of administration, dose, administration time, etc.) should be completely recorded in the original data, eCRF.

1) Routine medications for eye operation: Fluorescein Sodium, Indocyanine Green, local anesthetics (including retrobulbar anesthetics for avoiding eye movement), local antibiotics, mydriatic agents;

2) Medications for preventing nausea caused by injection of Fluorescein Sodium and Indocyanine Green;

3) Medications or therapies required for other past diseases;

4) Other disease-related supportive therapies;

5) The investigator may give appropriate treatment for adverse events occurring during the study.

**5.2.2 Prohibited concomitant therapies**

The following concomitant therapies are prohibited during the study, including the screening period.

1) Other medications for BCD (including Lucentis and Avastin, etc.);

2) Drugs with toxicity to lens, retina, and optic nerve, including Desferrioxamine, Chloroquine/Hydroxychloroquine, Tamoxifen, Phenothiazine, Ethambutol, etc.;

3) Surgery: Retinal laser therapy, periocular vascular bypass surgery, photodynamic therapy, macular foveal laser photocoagulation, vitrectomy, submacular surgery, cataract surgery, or other surgical intervention.

**5.2.3 Overdose**

Referring to the clinical study data of Luxturna (produced by Spark, intended for LCA patients carrying RPE65 gene mutation), the only gene replacement therapy marketed in the field of inherited retinal degeneration, and RPGR gene replacement therapy drug published in Nature Medicine in February 2020, overdose has the risk of causing local mild inflammatory reactions in the retina and corticosteroids can be given if necessary for effective control.

Overdose of investigational drug due to any condition should be truthfully recorded, its causes should be analyzed, taking corresponding actions to avoid recurrence.

**5.2.4 Rescue therapy**

There is no specific rescue medication or therapeutic measure for the investigational drug. In case of emergency in clinical practice, it can be closely observed and symptomatic treatment can be given according to the applicable clinical diagnosis and treatment process.

**5.2.5 Recording of concomitant medications**

Concomitant medications refer to all medications (including traditional Chinese medicines) administered, except for investigational drug and are recorded as follows: Generic name, indication, dose, usage, start and end time of treatment, etc.

# 6. Study Flow and Study Procedure

## 6.1 Study Flow

### 6.1.1 Screening baseline visit

The following contents should be completed during the screening period.

### (V1, 1 week pre-op)

1) Sign informed consent form

It must be performed before all screening tests; informed consent form must be signed before the subject is enrolled in the study and before any protocol-specified procedures are performed. Each subject will be given a unique subject identification number (subject screening number) when obtaining the informed consent form.

2) Collect demographic data:

Data including gender, age, ethnicity and other information should be collected during the screening period. The study personnel must photocopy the subject's identification card, record the mailing address, contact number, emergency contact person and contact number, and these original records shall be retained at the study site only.

3) Collect medical history and treatment history

Detailed information should be obtained during the screening period about the subject's history of ophthalmological diseases, treatment history, medical history of other major organs, including past medical history, menopause history, surgical history, smoking and drinking history, and allergy history, and the use of all medications within 3 months prior to screening should be recorded.

4) Verification of inclusion and exclusion criteria

5) Physical examination

6) Vital signs

7) ECG and chest X-ray

8) Laboratory tests: Blood routine/urine routine/blood chemistry; Serum virology tests; coagulation function; serum pregnancy test;

9) Biological sample collection and testing: Collection of tear, peripheral blood leukocytes and peripheral blood mononuclear cells, detection of rAAV vector neutralizing antibodies in peripheral blood plasma and CYP4V2 protein antibodies in peripheral blood serum

10) General ophthalmological examination: Including intraocular pressure, slit-lamp examination and ophthalmoscopy

11) BCVA (best-corrected visual acuity) assessment

12) Color fundus photography and FAF

13) OCT (optical coherence tomography)

14) Color vision test

15) Macular microperimetry

16) Contrast sensitivity test

17) mfERG examination

18) MLMT behavioral test

### 6.1.2 Observation period

V2 (D-3), the following items should be completed:

1) Prednisone is administered orally at a dose of 1 mg/kg/day;

2) Adverse events, concomitant medications, treatments

V3 (D0), the following items should be completed:

1) Vital signs (within 1 h pre-dose and 1 h ± 15 min, 3 h ± 30 min post-dose)

2) Prednisone is administered orally at a dose of 1 mg/kg/day

3) Subretinal injection

4) ECG (3 h ± 30 min post-dose)

5) Biological sample collection and testing (3 h ± 30 min post-dose): Collection of tear and peripheral blood leukocytes

6) Adverse events, concomitant medications, treatments

V4 (D1), the following items should be completed:

1) Physical examination

2) Vital signs

3) ECG

4) Laboratory tests: Blood routine/urine routine/blood chemistry; Serum virology tests; coagulation function;

5) Biological sample collection and testing: Collection of tear and peripheral blood leukocytes

6) General ophthalmological examination: Including intraocular pressure, slit-lamp examination and ophthalmoscopy

7) BCVA assessment

8) Color fundus photography and FAF

9) OCT (optical coherence tomography)

10) Prednisone is administered orally at a dose of 0.5mg/kg/day

11) Adverse events, concomitant medications, treatments

V5 (D2), the following items should be completed:

1) Vital signs

2) Biological sample collection: Collection of lacrimal fluid

3) General ophthalmological examination: Including intraocular pressure, slit-lamp examination and ophthalmoscopy

4) BCVA (best-corrected visual acuity) assessment

5) Color fundus photography and FAF

6) OCT (optical coherence tomography)

7) Prednisone is administered orally at a dose of 0.5 mg/kg/day

8) Adverse events, concomitant medications, treatments

V6 (D3), the following items should be completed:

1) Vital signs

2) Biological sample collection and testing: Collection of tear

3) General ophthalmological examination: Including intraocular pressure, slit-lamp examination and ophthalmoscopy

4) BCVA (best-corrected visual acuity) assessment

5) Color fundus photography and FAF

6) OCT (optical coherence tomography)

7) Prednisone is administered orally at a dose of 0.5mg/kg/day

8) Adverse events, concomitant medications, treatments

V7 (D7), the following items should be completed:

1) Prednisone is administered orally at a dose of 0.5 mg/kg/day, last dose

2) Vital signs

3) ECG

4) Laboratory tests: Blood routine/urine routine/blood chemistry; Serum virology tests; coagulation function;

5) Biological sample collection and testing: Collection of tear and peripheral blood leukocytes

6) Adverse events, concomitant medications, treatments

V8 (D14 ± 2d), the following items should be completed:

1) Vital signs

2) ECG

3) Laboratory tests: Blood routine/urine routine/blood chemistry;

4) Biological sample collection and testing: Collection of peripheral blood mononuclear cells, detection of rAAV vector neutralizing antibodies in peripheral blood plasma and CYP4V2 protein antibodies in peripheral blood serum

5) General ophthalmological examination: Including intraocular pressure, slit-lamp examination and ophthalmoscopy

6) BCVA (best-corrected visual acuity) assessment

7) Color fundus photography and FAF

8) OCT (optical coherence tomography)

9) Adverse events, concomitant medications, treatments

V9 (D28 ± 5d), the following items should be completed:

1) Physical examination

2) Vital signs

3) ECG and chest X-ray

4) Laboratory tests: Blood routine/urine routine/blood chemistry; Serum virology tests; coagulation function;

5) Biological sample collection and testing: Collection of peripheral blood mononuclear cells, detection of rAAV vector neutralizing antibodies in peripheral blood plasma and CYP4V2 protein antibodies in peripheral blood serum

6) General ophthalmological examination: Including intraocular pressure, slit-lamp examination and ophthalmoscopy

7) BCVA (best-corrected visual acuity) assessment

8) Color fundus photography and FAF

9) OCT (optical coherence tomography)

10) Color vision test

11) Macular microperimetry

12) Contrast sensitivity test

13) mfERG examination

14) MLMT behavioral test

15) Adverse events, concomitant medications, treatments

V10 (D60 ± 5d), the following items should be completed:

1) Vital signs

2) ECG

3) Laboratory tests: Blood routine/urine routine/blood chemistry

4) General ophthalmological examination: Including intraocular pressure, slit-lamp examination and ophthalmoscopy

5) BCVA (best-corrected visual acuity) assessment

6) Color fundus photography and FAF

7) OCT (optical coherence tomography)

8) Color vision test

9) Macular microperimetry

10) Contrast sensitivity test

11) mfERG examination

12) MLMT behavioral test

13) Adverse events, concomitant medications, treatments

V11 (D90 ± 5d), the following items should be completed:

1) Physical examination

2) Vital signs

3) ECG

4) Biological sample collection and testing: Detection of rAAV vector neutralizing antibodies in peripheral blood plasma and CYP4V2 protein antibodies in peripheral blood serum

5) General ophthalmological examination: Including intraocular pressure, slit-lamp examination and ophthalmoscopy

6) BCVA (best-corrected visual acuity) assessment

7) Color fundus photography and FAF

8) OCT (optical coherence tomography)

9) Adverse events, concomitant medications, treatments

V12 (D180 ± 30d), the following items should be completed:

1) Vital signs

2) ECG

3) Laboratory tests: Blood routine/urine routine/blood chemistry

4) General ophthalmological examination: Including intraocular pressure, slit-lamp examination and ophthalmoscopy

5) BCVA (best-corrected visual acuity) assessment

6) Color fundus photography and FAF

7) OCT (optical coherence tomography)

8) Color vision test

9) Macular microperimetry

10) Contrast sensitivity test

11) mfERG examination

12) MLMT behavioral test

13) Adverse events, concomitant medications, treatments

V13 (D270 ± 30d), the following items should be completed:

1) Vital signs

2) ECG

3) General ophthalmological examination: Including intraocular pressure, slit-lamp examination and ophthalmoscopy

4) BCVA (best-corrected visual acuity) assessment

5) Color fundus photography and FAF

6) OCT (optical coherence tomography)

7) Adverse events, concomitant medications, treatments

V14 (D365 ± 30d), the following items should be completed:

1) Physical examination

2) Vital signs

3) ECG and chest X-ray

4) Laboratory tests: Blood routine/urine routine/blood chemistry; Serum virology tests; coagulation function;

5) Biological sample collection and testing: Collection of tear, peripheral blood leukocytes and peripheral blood mononuclear cells, detection of rAAV vector neutralizing antibodies in peripheral blood plasma and CYP4V2 protein antibodies in peripheral blood serum

6) General ophthalmological examination: Including intraocular pressure, slit-lamp examination and ophthalmoscopy

7) BCVA (best-corrected visual acuity) assessment

8) Color fundus photography and FAF

9) OCT (optical coherence tomography)

10) Color vision test

11) Macular microperimetry

12) Contrast sensitivity test

13) mfERG examination

14) MLMT behavioral test

15) Adverse events, concomitant medications, treatments

### 6.1.3 Follow-up period

V15 (15 months ± 30 days after the end of observation period), the following items should be completed:

1) Physical examination

2) Vital signs

3) ECG and chest X-ray

4) Laboratory tests: Blood routine/urine routine/blood chemistry; Serum virology tests; coagulation function;

5) Biological sample collection and testing: Collection of tear, peripheral blood leukocytes and peripheral blood mononuclear cells, detection of rAAV vector neutralizing antibodies in peripheral blood plasma and CYP4V2 protein antibodies in peripheral blood serum

6) General ophthalmological examination: Including intraocular pressure, slit-lamp examination and ophthalmoscopy

7) BCVA (best-corrected visual acuity) assessment

8) Color fundus photography and FAF

9) OCT (optical coherence tomography)

10) Color vision test

11) Macular microperimetry

12) Contrast sensitivity test

13) mfERG examination

14) MLMT behavioral test

15) Adverse events, concomitant medications, treatments

In case of premature termination of the study, the following items should be completed:

1) Vital Signs and Physical Examination

2) Laboratory tests: Blood routine/urine routine/blood chemistry

3) 12-Lead ECG and chest X-ray

4) General ophthalmological examination

5) Color fundus photography and FAF

6) OCT

7) Macular microperimetry, contrast sensitivity, mfERG, MLMT

8) Biological sample collection and testing: Collection of tear, peripheral blood leukocytes and peripheral blood mononuclear cells, detection of rAAV vector neutralizing antibodies in peripheral blood plasma and CYP4V2 protein antibodies in peripheral blood serum

9) Adverse events, concomitant medications, treatments.

Comments:

1) The test items during the study are detailed in Appendix 3.

2) Sample collection, processing and shipment procedures during the study are detailed in Sample Management Manual.

3) Biological sample collection time windows are detailed in Sample Management Manual.

4) During the study, in order to protect the safety of subjects, the investigator may increase the safety-related study procedure or examination number of such measures according to the actual situation, instead of limiting to the examination frequency specified in the study flow, and the examination results will be recorded in the subject's original documents.

## 6.2 Study Procedure

### 6.2.1 Sign informed consent form

Informed consent form must be signed before the subject is enrolled in the study and before any protocol-specified procedures are performed. Each subject will be given a unique subject identification number (subject screening number) when obtaining the informed consent form.

Before signing the informed consent form, the investigator or designated study personnel should give the subject sufficient time and opportunity to understand the details of the study and answer all questions related to the study raised by the subject in detail.

During the informed consent process, the investigator must comply with regulatory requirements of the drug regulatory authority, the Declaration of Helsinki and local regulations.

During the informed consent process, if the subject or his/her legal representative lacks reading ability, an impartial witness must assist and witness the informed consent.

No written or oral information related to the study shall be used in any language that causes the subject and his/her legal representative to waive his/her legal rights and interests, nor shall it contain any language that exempts the investigator and his/her medical institution, sponsor and his/her agent from their responsibilities.

The investigator should explain the contents of the informed consent form and other written materials to the subject or his/her legal representative and witness in detail. If the subject or his/her legal representative orally agrees to participate in the study, he/she should sign the informed consent form, and the witness must sign and date the informed consent form to prove that the subject or his/her legal representative has accurately explained the informed consent form and other written materials by the investigator, understands the relevant contents, and agrees to participate in the clinical study.

The subject or his/her legal representative shall receive a copy of signed and dated informed consent form and other written materials provided to the subject; during the study, the subject or his/her legal representative shall receive a copy of the updated informed consent form signed and dated, as well as the revised text of other written materials.

When the legal representative gives informed consent on behalf of the subject, the subject should be informed and helped understand the relevant information of the clinical study as far as possible, and the subject should personally sign and date the informed consent form as far as possible.

### 6.2.2 Collection of demographic data

Data including gender, age, ethnicity and other information of subjects should be collected during the screening period. The study personnel must photocopy the subject's identification card, record the mailing address, contact number, emergency contact person and contact number, and these original records shall be retained at the study site only.

### 6.2.3 Collection of medical history and treatment history

Collect the ophthalmic medical history, ophthalmologic treatment history, systemic and other vital organ medical history and surgical history, smoking and drinking history and allergic history of subjects, and record the use of all drugs within 6 months prior to screening.

### 6.2.4 Verification of inclusion and exclusion criteria

Collect the clinical data and genetic diagnosis results of patients, and confirm that patients meet the inclusion criteria of this study according to the inclusion criteria and exclusion criteria, and there are no conditions listed in the exclusion criteria.

### 6.2.5 See Appendix 3 for the test items during the study.

### 6.2.6 See Sample Management Manual for sample collection, processing and shipment procedures during the study in details.

### 6.2.7 See Sample Management Manual for biological sample collection time windows in details.

### 6.2.8 Documentation of concomitant medications

Concomitant medications refer to all medications (including traditional Chinese medicines) administered, except for investigational drug and are recorded as follows: generic name, indication, dose, usage, start and end time of treatment, etc.

At the screening visit, the investigator should ask the subject in detail about the treatment for ophthalmic diseases prior to screening and the use of all medications or therapies within 3 months prior to screening to ensure that the subject meets all inclusion and none of the exclusion criteria, and record the information obtained in the eCRF. Also, long-term medications taken by the subject at screening for chronic disease should be recorded.

During the observation period and at subsequent visits during the observation period, the investigator should carefully ask and record the recent medications or therapies received by the subject. If there is any change in dose or other of long-term medication taken by a subject, the reason for the change and details should be recorded in the eCRF. If a subject needs to take any new medication, he/she should consult the investigator as timely as possible before taking the medication. If the subject fails to reach the investigator in time for special reasons, he/she should inform the investigator faithfully at the next visit at the latest.

# 7. Study Evaluation

## 7.1. Safety Evaluation

Safety evaluation includes adverse events, vital signs, physical examination, ophthalmological examination, laboratory examination, ECG and immunogenicity.

1) Adverse events: Ocular hypertension (excluding slightly high intraocular pressure within 24 hours postoperative), endophthalmitis, vitreous hemorrhage, subretinal hemorrhage, retinal detachment (excluding within 14 hours postoperative), macular hole;

2) Ophthalmological examination: Visual acuity test, intraocular pressure test (intraocular pressure in both eyes), slit-lamp examination, ophthalmoscopy, color fundus photography and OCT;

3) Vital signs, physical examination, chest X-ray and ECG;

4) General laboratory tests: Blood routine and urine routine, liver function and renal function tests, serum virology tests, coagulation function test.

5) Drug-time curves and mean drug-time curves are plotted for each subject based on rAAV vector DNA concentrations measured in lacrimal fluid and peripheral blood leukocytes at each time point.

6) Immune-time curves are plotted for each subject based on cellular and humoral immune data measured for the therapeutic vector in the blood of subjects in the study.

In addition to observation of systemic adverse events/reactions, the focus is on ocular adverse events/reactions. Criteria for grading ocular adverse events are shown in Appendix 1. Definition of serious (sight-threatening) ocular adverse events is detailed in Appendix 2. Ocular adverse events should be assessed as injection-related complications or drug-related.

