| **Sample Size:** 3 + 9 expected |
| **Study Procedure:**  Eligible subjects will be administered prednisone 3 days (Day -3) prior to dosing for 10 days at a dose of 1 mg/kg/day for the first 3 days. On the day of ZVS101e administration, vitrectomy is performed on the target eye according to the clinical practice, and 150 uL of the ZVS101e is injected into the subretinal space through a sterile injection needle for single use in strict accordance with the package insert of the drug. After surgery, routine treatment after vitrectomy is performed and prednisone is orally administered at 0.5 mg/kg/day for an additional 7 days without any treatment in the fellow eye. Patients have to lie supine for at least 14 hours following treatment (according to the clinical study results of Luxturna, 150 uL of the treatment vector was completely absorbed approximately 14 hours after local injection).  On D1, D2, D3, D7, D14, D28, D60, D90, D180, D270 and D365 after injection and at 15 months after the end of observation period, safety assessments were performed at corresponding time points, adverse events and concomitant medications are recorded for safety evaluation.  According to the blood collection points, biological samples are collected for relevant safety and immunogenicity evaluation.  Ocular functional tests (BCVA- ETDRS chart, macular microperimetry, mfERG, dark-adapted contrast sensitivity, and MLMT) and morphological test (color fundus photography, fundus autofluorescence (FAF) and OCT) are performed at visit points during the study to preliminarily evaluate the efficacy of the vector. |

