| **Safety** **Evaluation:**  1) Adverse events: Ocular hypertension (excluding intraocular pressure slightly higher within postoperative 24 hours), endophthalmitis, vitreous hemorrhage, subretinal hemorrhage, retinal detachment (excluding within postoperative 14 hours), macular hole;  2) Ophthalmological examination:BCVA, intraocular pressure test (IOP, intraocular pressure in both eyes), slit-lamp examination, ophthalmoscopy, color fundus photography, FAF and OCT;  3) Vital signs, physical examination, chest X-ray and ECG;  4) General laboratory tests: Blood routine and urine routine, liver function and renal function tests, Serum virology tests, coagulation function test;  5) Vector shedding: Each subject was evaluated according to the concentration of rAAV vector DNA detected in tear and peripheral blood leukocytes.  6) Immunogenicity-: Each subject was evaluated based on cellular and humoral immune response against the therapeutic vector in the blood. |

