# 2. Study Objectives

**Primary Objective:** To evaluate the safety of a single subretinal injection of rAAV2/8-hCYP4V2 in patients with Bietti's crystalline dystrophy (BCD).

**Secondary Objective:** To preliminarily explore the clinical efficacy of rAAV2/8-hCYP4V2 gene replacement therapy.

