## 3.2 Rationale for Dose Setting

The investigational drug rAAV2/8-hCYP4V2 Ophthalmic Injection is a gene replacement therapy. In preliminary safety clinical study (ClinicalTrials No.: NCT04722107), enrollment, administration, and 3-month safety and efficacy observation have been completed for 3 subjects. During the observation period, no drug- or treatment-related serious adverse reactions occurred in any of the 3 subjects; meanwhile, 2 of the subjects showed significant improvements in visual acuity and MLMT score. It can be seen that the clinical dose of 5×10^8^ vg/uL has good safety and reflects certain efficacy.

Preclinical pharmacodynamic experiment has preliminarily demonstrated that 1 uL of the following concentrations of rAAV2/8-hCYP4V2 were injected into the subretinal space of CYP4V2 knockout mice: CYP4V2 protein was expressed in 1×10^8^, 5×10^8^, 1×10^9^, 3×10^9^, 6×10^9^ and 1×10^10^ (unit: vg/uL), and the 6-month in vivo observation at following three doses of 3×10^9^ vg, 6×10^9^ vg and 1×10^10^ vg showed that 3×10^9^ vg had a significant therapeutic effect without obvious toxicities, and 6×10^9^ vg and 1×10^10^ vg had evident efficacy in the early stage, but obvious retinal toxicity in the later stage.

Referring to Luxturna (produced by Spark, intended for LCA patients carrying RPE65 gene mutation), the only gene replacement therapy marketed in the field of inherited retinal degeneration, the dose escalation concentration of Luxturna is designed as: 1×10^8^ (150 uL), 3.2×10^8^ (150 uL) and 5×10^8^ (300 uL) (unit: vg/uL). The dose escalation study results showed that all of the above three concentrations had therapeutic effect without obvious toxicities. The recommended Phase 3 concentration of Luxturna was 5×10^8^ vg/uL (300 uL), which was the maximum concentration tested in vivo.

Referring to the clinical study data of RPGR gene replacement therapy drug published in Nature Medicine in February 2020, the dose escalation concentrations were designed as six doses: 5×10^7^ (40-100 uL), 1×10^8^ (40-100 uL), 5×10^8^ (30-100 uL), 1×10^9^ (60-100 uL), 2.5×10^9^ (50-150 uL) and 5×10^9^ (30-80 uL) (unit: vg/uL). The results showed that 5×10^7^ vg/uL and 1×10^8^ vg/uL groups had no significant improvement, 5×10^8^ vg/uL group had significant increase, and 7 of 9 subjects in the three high concentration groups showed mild inflammatory reaction, which could be effectively managed after hormone therapy.

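### The 14-hour exclusion removes every retinal detachment by time alone, not only the intended bleb, conflicts with section 8.1, and leaves the clock undefined

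*Protocol*

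**What the plan says.** Section 7.1 of the protocol (Safety Evaluation) opens with a short list of ocular adverse events, which includes "retinal detachment (excluding within 14 hours postoperative), macular hole". The safety evaluation part of the synopsis carries the same rule: "retinal detachment (excluding within postoperative 14 hours), macular hole". Neither place names a cause, a location or a type of detachment.

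The study procedure part of the synopsis describes the setting: "vitrectomy is performed on the target eye according to the clinical practice, and 150 uL of the ZVS101e is injected into the subretinal space". It then asks for at least 14 hours supine and supports this with a result from the marketed RPE65 product, that "150 uL of the treatment vector was completely absorbed approximately 14 hours after local injection". No other 14-hour figure appears in the protocol.

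Section 8.1 defines an adverse event broadly, as anything untoward that happens to a patient during the study, related or not, with no time limit. Section 9.3.3 plans the incidence of adverse events overall and by kind. Section 2 makes safety the primary objective.

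**The concern.** A subretinal injection lifts the retina on purpose, so some rule is needed to keep the expected bleb out of the detachment count. A clock does this badly, because a bleb and a detachment from a tear or from the surgery can both be present in the same hours. The ocular hypertension exclusion in the same list combines a time with a degree: only a slight rise in the first 24 hours is left out. The detachment exclusion has the time and nothing else.

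Detachment is among the complications that a reader of a vitrectomy and subretinal injection study will look for first. If the listed event can omit a surgical detachment, or include an expected bleb, the reported rate does not mean what it appears to mean. With so few eyes, a single case decides whether the report says none or one.

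**Working it through.** The protocol states no detachment rate, power or formula, so there is no figure to reproduce. The check compares the texts and then sizes one misclassified eye.

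**1. Origin of the clock.** The 14 hours in 7.1 matches only the absorption time in the synopsis. That time is approximate and comes from another product at the same volume, 150 uL. The protocol does not state the link; it is an inference, and the most natural one.

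**2. Schedule.** Under "V3 (D0), the following items should be completed" in section 6.1.2, the list holds vital signs, prednisone, the injection, an ECG, samples, and the recording of adverse events and concomitant treatment. It contains no eye examination. The first scheduled ophthalmoscopy, fundus photography and OCT after surgery are at V4 (D1), and they are repeated on D2 and D3. No clock time is fixed for D1. With at least 14 hours supine, D1 imaging would usually fall after the cut-off, but that is an assumption.

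**3. Section 7.1 against section 8.1.** Take a detachment from a surgical tear, seen a few hours after the operation. Under 8.1 it is an adverse event. Under 7.1 it is excluded from the named list. Section 9.3.3 does not say which definition governs the incidence tables.

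**4. What is being timed.** The text could mean any of three things. I take the window to include the operation itself, which the wording also leaves open.

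| Reading of the 14 hours | True surgical detachment in the first hours | Bleb not yet absorbed at D1, after hour 14 |
|---|---|---|
| Onset | Excluded, even if still present at D1 | Excluded, since it starts at injection |
| First detection | Excluded if seen within the window; counted if first seen later | Could be counted, if detection means the first recorded examination finding |
| Presence | Counted if still there after hour 14; lost only if found and resolved earlier | Could be counted |

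Each reading permits at least one misclassification. Both can arise in full only under first detection.

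**5. Size of one eye.** Section 9.1.2 gives 3 + 9 = 12 subjects, one target eye each. Section 9.3.1 sets 95% confidence; the exact (Clopper-Pearson) interval is my choice.

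- Step in the rate: 1/12 = 8.3 percentage points; for the 9 new subjects alone, 1/9 = 11.1 points.
- 0/12: upper limit 1 − 0.025^(1/12) = 26.5%.
- 1/12: the upper limit p solves (1 − p)^12 + 12p(1 − p)^11 = 0.025, giving p = 38.5%. The interval is 0.2% to 38.5%.
- For 9 eyes: 0/9 has upper limit 33.6%; 1/9 has 48.2%.

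**The case against.** The best defence is that nothing need be lost. Section 8.1 has no time exclusion, the recording instructions there ask for any untoward sign, and section 9.3.3 analyses all adverse events, not only the list in 7.1. A detachment still present on D1 would meet ophthalmoscopy, photography and OCT that day. The clause reaches only what is seen at surgery or in an unscheduled look in the first hours, and the intended bleb is present then too. Appendix 1 (grading) and Appendix 2 (serious ocular events) are not shown and might define types of detachment.

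Much of this stands. It makes the loss of a surgical detachment a possibility and not a certainty. It does not remove the defect, because 7.1 and 8.1 give different answers for the same eye and the protocol does not say which one prevails. Under the onset reading, a surgical detachment remains excluded from the list even when the D1 images show it.

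It is also fair to say that slow absorption of the bleb is not shown. The one figure in the protocol has the same volume fully absorbed at about 14 hours, and an intended bleb is hardly an untoward event under 8.1. That side of the problem is a gap in the wording, not a predicted occurrence.

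**Conclusion.** The point holds as a defect in an outcome definition. The exclusion is written as a time and covers all detachments. Its apparent purpose is narrower, it conflicts with section 8.1, and the thing being timed is not stated. By onset or first detection, a surgical detachment in the first hours can drop out of the named safety events. By presence or first detection, a bleb not absorbed at D1 could be counted. One eye is worth 8.3 points with 12 eyes, or 11.1 with 9. These figures show what one case would do, not how likely it is.

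Four stronger readings are tempting and are not supported:

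- A reader might infer that the rule always errs in both directions. That holds in full only if first detection governs.
- A reader might infer that true surgical detachments will go unreported. Section 8.1 could still capture them. The protocol also names no formal primary endpoint, only a primary safety objective.
- A reader might infer that blebs will still be visible on D1 to D3. No figure in the documents says so, and a persisting bleb would be one event in one eye however many images showed it.
- A reader might infer that intraocular inflammation would be missed because the list does not name it in general. Section 8.1 and the scheduled slit-lamp examinations already cover it, so naming it is only a preference.

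The conclusion assumes that the unseen appendices do not already separate the bleb from other detachments.

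**What to change.** In section 7.1 and the synopsis, replace the clock with a type. Exclude only the intended subretinal bleb at the injection site. Count any other retinal detachment as an adverse event whatever its time of onset, including during surgery. State in section 8.1 that the same definition applies, so that the listed events and the incidence tables in 9.3.3 agree. Check Appendices 1 and 2 against it.

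Classify each case from the operative record, together with the ophthalmoscopy, OCT and fundus photographs already scheduled on D1 to D3. No imaging is planned on D0, so the operative record has to note the bleb site and any retinal break for this to work.

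The cost is protocol wording and one eCRF field, with no new visit. The reported detachment rate may come out somewhat less favourable.
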